**Objective:**

We aimed to assess the efficacy of FiberMore in improving the dietary fiber intake of T2D patients by conducting a pilot randomized controlled trial. In addition, we want to explore the efficacy of FiberMore in reducing HbA_1c_ of T2D patients via improvement in dietary fiber intake.

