### Secondary Outcomes Analysis

We will perform analysis of covariance on the change of HbA_1c_ from the time consent is obtained to the end of the intervention period (at 12 weeks) or the end of the observation period (at 24 weeks), using the measurements at the time consent is obtained as covariates. The estimated mean change in each group and its 2-sided 95% CI will be calculated. Additionally, the estimated difference between groups and its 2-sided 95% CI will be calculated. The proportion of HbA_1c_ less than 7% at week 12 (E3) and week 24 (E4; or point of discontinuation, if earlier) will be compared between groups by the Fisher exact test.

The change from baseline in the clinical laboratory test values stated below at week 12 (E3) and week 24 (E4) (or point of discontinuation, if earlier) will be analyzed as the secondary outcomes:

 Weight (kg) BMI (kg/m^2^) Systolic and diastolic blood pressure (mmHg) Estimated glomerular filtration rate (ml/min/1.73 m^2^) Fasting blood glucose (mg/dL) Low-density lipoproteincholesterol (LDL-C; mg/dL) High-density lipoproteincholesterol (HDL-C; mg/dL) Triglyceride (mg/dL)

The percentages of participants at each stage of the transtheoretical model (TTM) stage of change will be calculated for both groups at the end of the intervention period (week 12) and the end of the observation period (week 24) were compared between groups using the Cochran-Mantel-Haenszel test.

Between-group changes in all TPB survey elements for dietary fiber, salt, and saturated fat intake (attitude, subjective norms, PBC, and intention) will be analyzed from the time of run-in to the end of 10 weeks, and to the end of the observation period (24 weeks), using repeated measures ANOVA with time (Week 1, Week 10, and Week 24) as a within-subjects factor and group (control vs intervention) as a between-subjects factor.

Changes in diabetes medications since consent acquisition at the end of the intervention period (at 12 weeks) and at the end of the observation period (at 24 weeks; classified as intensified, unchanged, and weakened) will be calculated for each group and compared between groups using the Cochran-Mantel-Haenszel test. The proportion of new medications added will be compared between groups by the Fisher exact test.

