We will also calculate the percentage of responses for each option on the Likert scale and for the “Yes or No” scale in “Survey on participants’ satisfaction and perceived usefulness of the intervention” at the end of the intervention period for both intervention group and control group. For the “Survey on intention to improve eating habits using a Generative AI-enabled app”, we will calculate the percentage of responses for each option on the Likert scale at the end of the observation period for the intervention group.

As part of our exploratory analysis, we will assess the reliability of the TPB questionnaire using the Cronbach α coefficient. Additionally, we will conduct multivariate regression analyses to examine various associations related to the TPB constructs. Specifically, we will investigate the relationship between changes in intention (INT) to increase fiber intake and changes in fiber intake outcomes both between and within groups. Furthermore, we will analyze the associations between changes in attitude (ATT), subjective norms (SN), and PBC with changes in intention to increase fiber intake, as well as the relationship between changes in PBC and changes in fiber intake outcomes at both the between-group and within-group levels. The impact of the intervention on INT via ATT, SN, and PBC will be evaluated through mediation analysis.

We will calculate the frequency and weekly percentages of the following measurements during the intervention period in the intervention: number and percentage of days fiber goal is met out of 7 days, the number and percentage of implemented solutions in a week, the average weekly fiber change in the intervention group from run-in, and the average weekly energy change in the intervention group from run-in. We will also evaluate the effects of changes in dietary fiber intake on changes in BMI and HbA_1c_ using the Pearson correlation test and simple regression analysis.

We will perform a statistical analysis of safety outcomes by calculating the number and percentage of individuals who experience adverse events during run-in, intervention, and observation periods. During the intervention and observation periods, data will be compiled separately for the intervention and control group, and the percentages will be compared between groups using the Fisher exact test.

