Another key aspect of our approach is focusing exclusively on patients who are already motivated to change their behavior in dietary fiber intake. We achieve this by filtering participants based on their stage of change in TTM, targeting those in the contemplation, preparation, and action stages, which has shown to be effective [20,60]. Individuals who are already motivated to change need guidance and support to enhance their intentions and to translate their intentions into action, and they are more likely to engage with self-management tools [61]. In contrast, individuals with low motivation would require a fundamentally different intervention focused on enhancing motivation. Our strategy is supported by a study that reported 93.7% of T2D patients in Japan fall within these stages of dietary behavior change [62], suggesting that our intervention approach applies to a very large group of potential participants.

The study will maintain usual care practices for both the intervention and control groups. There will be no restrictions on medication adjustments or concurrent treatments during the study period. The intervention is aimed exclusively at improving dietary fiber intake, complementing the dietary counseling that T2D patients typically receive as a standard care practice in Japan.

This study is a multicenter randomized controlled trial, which enhances the generalizability of the findings to individuals with T2D across Japan. The elements of the intervention, such as the use of an AI-enabled chatbot to carry out personalized goal setting, barrier-solution planning, and meal logging are not unique to the Japanese context and can be adapted to other settings.

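### The exploratory fiber–HbA1c/BMI analysis uses an unadjusted one-predictor model, does not say which arms it uses, and calls the result an effect

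*Protocol article*

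**What the plan says.** The abstract's Objective adds to the main aim a wish to explore whether FiberMore lowers HbA1c "of T2D patients via improvement in dietary fiber intake". The analysis that bears on that pathway is one sentence near the end of Secondary Outcomes Analysis, which opens "We will also evaluate the effects of changes in dietary fiber intake on changes in BMI". It treats HbA1c in the same way, and the method stated for both outcomes is "using the Pearson correlation test and simple regression analysis". It names no covariate and no analysis group. The sentence before it lists measures for the intervention group only, including "the average weekly fiber change in the intervention group from run-in".

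Other parts of the plan bear on this:

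- Primary Outcome Analysis adjusts fiber change for run-in fiber, and Secondary Outcomes Analysis adjusts HbA1c change for the value at consent.
- Medication change is recorded, "classified as intensified, unchanged, and weakened", and compared between arms as an outcome of its own.
- The Discussion states: "There will be no restrictions on medication adjustments or concurrent treatments during the study period".
- Mediation is planned for intention only: "The impact of the intervention on INT via ATT, SN, and PBC will be evaluated through mediation analysis".
- The same section says secondary and exploratory results will be treated as exploratory.

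**The concern.** Simple regression has a single predictor, so the choice of estimator is fixed here and is not a detail left for the SAP. Three things that can move HbA1c or BMI alongside fiber are left out.

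- **Baseline values.** Entry requires HbA1c of at least 7.5% and run-in fiber below 20 g, so both change scores start from selected values and can depend on baseline. The plan adjusts for baseline when it analyses each change alone, but not when it relates one to the other.
- **Drug changes.** Every participant starts above the below-7% treatment target that the Discussion cites, and drug adjustment is free. If those whose drugs change also differ in fiber change, the slope absorbs part of the drug effect.
- **Arm, if both arms are used.** FiberMore also brings goal setting, fiber-to-energy feedback, barrier planning and 12 weeks of logging, while controls log only in weeks 11 and 12. Routes to HbA1c other than fiber are plausible.

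This is the only listed analysis that links fiber change to HbA1c. The HbA1c ANCOVA tests the arm effect, not the fiber pathway. A biased slope described as an effect could be carried into the design of a later trial.

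**Working it through.** **Inputs from the protocol.** Sample Size Consideration gives a difference of δ = 7 g, an SD of fiber change of 9.85 g, two-sided 5% and 80% power. Allocation is 1:1, and Results reports 72 randomized.

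**Reproducing the plan's figure.** The normal approximation gives 2 × (1.960 + 0.842)² × 9.85² / 7² = 31.1, so 32 per group. The noncentral t gives 79.9% power at 32 and 81.1% at 33, so the stated 33 reproduces. This confirms that 9.85 g is used as the within-arm SD. The plan gives no figure for the fiber–HbA1c regression.

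**Arm bias if arms are pooled.** Let HbA1c change = b × fiber change + g × arm + error, where g is the arm effect by routes other than fiber. With 1:1 arms the simple slope has expectation b + g × (δ/4) / (δ²/4 + SD²).

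- δ²/4 = 12.25 and SD² = 97.02, which sum to 109.27.
- Share of g credited to fiber over 7 g: 12.25 / 109.27 = 11.2%.
- The documents give no g. For assumed g of −0.1, −0.3 and −0.5 points, the bias is −0.0016, −0.0048 and −0.0080 per g, or −0.011, −0.034 and −0.056 points over 7 g.
- Range over assumed SDs: 12.25 / 61.25 = 20% at SD 7 g and 12.25 / 37.25 = 33% at SD 5 g. For g = −0.3 these are −0.06 and −0.10 points.
- If the true arm difference were 4 g at SD 9.85 g: 4 / 101.02 = 4.0% over 4 g.

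A simulation used 20,000 runs, N = 72 and an assumed residual HbA1c SD of 0.8. With b = 0 and g = −0.3 it gave a mean pooled slope of −0.0048 per g and 7.8% false positives, against 0.000 and 5.0% with an arm term. With a true slope of −0.02, the pooled mean was −0.025 for g = −0.3 and −0.015 for g = +0.3, so the bias runs either way. With intervention-group data only, g cannot enter.

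**Drug-change bias, under either reading.** Let a fraction p change drugs, with effect h on HbA1c and a difference m in mean fiber change between changers and others. The bias per g is h × p(1 − p) × m / variance of fiber change. All three inputs are assumptions: p = 10–30%, h = −0.5 to −1.0 points, m = ±4 g.

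- Pooled, smallest: 0.5 × 0.09 × 4 / 109.27 = 0.0016 per g, or 0.01 points over 7 g.
- Pooled, largest: 1.0 × 0.21 × 4 / 109.27 = 0.0077 per g, or 0.05 points over 7 g.
- One arm only (divisor 97.02): 0.18 / 97.02 × 7 = 0.01 to 0.84 / 97.02 × 7 = 0.06 points over 7 g.

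The sign follows m. An arm term does not remove this bias.

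**Baseline.** The size depends on how baseline HbA1c and baseline fiber relate to each other and to the two changes. The documents give no such figure, so none is put on it here.

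**The case against.** The sentence follows a list of intervention-only measures, so an intervention-only reading is at least as natural as a pooled one. A reader might infer that the analysis is pooled over arms, but the text does not say so, and under the other reading the whole arm component vanishes. This stands, and it is why the arm figure is conditional.

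A reader might also infer a large bias. With a within-arm SD of 3 g, more than half of a non-fiber arm effect would be credited to fiber (12.25 / 21.25 = 58%). Nothing in the protocol supports 3 g. The only SD it states is 9.85 g, and there the bias is small. A somewhat smaller SD is possible, because baseline intake is capped below 20 g and values are multi-day averages, but that is an assumption.

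Third, the formal Objective 2 compares HbA1c between arms and does not mention fiber as the route. It is served by a baseline-adjusted ANCOVA, and the fiber pathway is introduced in the abstract only as something to explore. This limits the weight of the point. It does not remove the confounding or justify describing an unadjusted slope as an effect.

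Finally, adjusting for medication change is not plainly better. It occurs after randomization, and physicians who see HbA1c at routine visits may act on it, so conditioning on it can itself bias the slope. This stands, and the variable should not go into the main model.

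**Conclusion.** The point holds in a limited form. The planned estimator is unadjusted, its population is not stated, and its wording claims more than it can deliver. It also departs from the plan's own practice of adjusting fiber change and HbA1c change for baseline. The size is modest: if arms are pooled, about 0.03 HbA1c points per 7 g at the protocol's inputs, given an assumed 0.3-point non-fiber arm effect; under either reading, roughly 0.01 to 0.06 points per 7 g in either direction from drug changes under the assumptions shown. The HbA1c effects, drug-change rates, fiber differences and residual SD are all assumed. The documents do not support a conclusion that the primary analysis or the HbA1c comparison between arms is compromised; neither uses this model.

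**What to change.** State which arms are analysed. Replace the correlation and simple regression with a linear regression of HbA1c (or BMI) change on fiber change, adjusted for the baseline value of the outcome and for run-in fiber, and for randomized arm if both arms are included. Report the slope with its 95% CI and call it an association.

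As a sensitivity analysis only, show the slope with and without adjustment for recorded medication change, or restricted to participants whose medication was unchanged. Note that medication change may itself respond to HbA1c.

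All variables are already collected, so the cost is a change of wording and a few lines of code. The downside is some precision: the arm-adjusted slope uses within-arm variation only, and at the protocol's inputs its standard error rises by about √(109.27 / 97.02) = 1.06, or 6%, for the same residual variance. The slope remains observational and can still be confounded, for example by energy intake or motivation.

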### Monitoring, Quality Control, and Data Management

An independent auditor, separate from the departments involved in this clinical trial, will inspect the medical institution and other relevant facilities to ensure that the trial is conducted in compliance with established protocols and standards.

In accordance with the EU Artificial Intelligence Act [50], FiberMore falls under the limited-risk category, as it delivers dietary advice and behavioral support but does not make clinical diagnoses or treatment decisions. We implemented a few measures to ensure that the dietary advice and behavioral support offered in FiberMore is safe for T2D patients. FiberMore has undergone pretesting and has been reviewed by a diabetes specialist on the research team to ensure its suitability for providing dietary advice to individuals with diabetes. The intervention development team has implemented safeguards to ensure that the chatbot’s conversations are suitable and reliable. For example, in the Learn More chatbot where users can get educational information, the chatbot discloses that “As I am a bot, I may rarely make mistakes, so please always use your common sense and follow your doctor’s instructions.” In addition, the chatbot conversations will be monitored by the study team daily to ensure that the advice given is safe and appropriate to T2D patients. If study participants encounter any unusual response from the chatbot at any time, they are advised to take a screenshot of the issue and send it to us by email, SMS text message, or Line, a popular social messaging app in Japan.

All data measured and provided through FiberMore will be securely transmitted to the research office’s backend system, which is hosted on Firebase, a cloud-based platform developed by Google on a password-protected computer through an internet connection and stored on the backend system. Firebase complies with major regulatory frameworks such as the General Data Protection Regulation and the California Consumer Privacy Act, meets international security and privacy standards including ISO/IEC 27001 (information security management) and ISO/IEC 27018 (protection of personally identifiable information in the cloud), and aligns with requirements under Japan’s Act on the Protection of Personal Information [51,52].

No personally identifiable information will be stored in the backend system alongside the study data, and all information will be pseudonymized using study participant ID. Data stored in the backend system include study participants’ ID, meal photos taken by study participants and photo timestamp, chat logs generated in FiberMore and its timestamp, feedback on nutritional information generated by AI on each logged meals, total daily intake and average weekly intake of energy, dietary fiber, and other nutrients (eg, protein, fat, carbohydrates, salt), daily fiber goal achievement status, daily implementation status of coping strategies (solutions), and content of weekly chosen barrier and coping strategies to increase fiber intake. All data on the backend system will be automatically backed up once a day across Google Cloud’s secure data centers. These backup copies can be restored in the event of system failure, accidental deletion, or data corruption.

Survey data from paper questionnaires are entered into the study database by a research co-investigator and independently verified by another research co-investigator to ensure data accuracy. Paper files are stored in locked cabinets within a locked room and are accessible only to authorized personnel. Paper questionnaires are stored in a locked room in locked cabinets and can be accessed only by authorized personnel.

TPB questionnaires administered using Jotform will be transmitted to the Jotform server, where the data is stored and accumulated. Jotform supports Health Insurance Portability and Accountability Act (HIPAA) compliance for managing sensitive health data, complies with GDPR for handling personal information, and aligns with the principles of Japan’s Act on the Protection of Personal Information [53]. Surveys administered via Jotform are pseudonymized using study participant ID. A research co-investigator will download the survey responses from the Jotform server into a password-protected folder on a computer in the Department of Planning, Information, and Management of The University of Tokyo Hospital for data analysis. To maintain data quality, participants with missing responses or inconsistencies on the TPB questionnaire such as extreme or contradictory answers to items assessing the same underlying construct will be asked to recomplete the relevant survey items.

### Ethical Considerations

This trial will be conducted in compliance with the Declaration of Helsinki, the Pharmaceutical and Medical Device Act, the Ministerial Ordinance on Good Clinical Practice for Medical Devices, and all other guidelines in relation to these regulations (jRCT2032240579). This study was approved by the institutional review board of the University of Tokyo School of Medicine (approval 2024442NI).

Before the start of the study, we provide clear explanations to the study participants using the consent explanation document. Written consent, based on the study participant’s free will, will be obtained. When obtaining consent, study participants will be given sufficient time and opportunities to ask questions, and all questions will be answered thoroughly. We also inform the study participants that their meal logs and chat conversations with the bot will be monitored by the research team for quality assurance and to improve the future iterations of the system. All patient data will be pseudonymized.

Study participants are free to withdraw consent at any point of the study, either pre- or postrandomization by contacting the research office in writing or via phone. We also inform the study participants that if consent is withdrawn before randomization, all the collected data will be discarded, while if consent is withdrawn after randomization, data collected up to the point of withdrawal will be retained.

As compensation for their participation, transportation costs to the research sites, phone internet data cost, and the time and effort required to complete the study procedures, study participants will receive a QUO card worth 30,000 yen (approximately US $200) after completing the 24-week observation period and the related questionnaires. This amount is considered reasonable for a 6-month clinical study in Japan. It is not intended as an inducement to participate but rather as a token of appreciation and to reduce financial barriers to participation.

All blood test and health examination results will be reviewed by the participant’s primary physician (also the recruiting physician) during routine visits, with results communicated to the participant during their outpatient consultation. If a study participant reports any concerning symptoms to the CRC, the CRC will consult the principal investigator, who is a diabetes specialist. If deemed necessary, the participant will be referred to their primary physician for further evaluation or care.

To ensure equal educational opportunities for all participants without influencing study outcomes, participants in the intervention group will receive a handout on salt reduction strategies at the postobservation (E4) meeting, while those in the control group will receive, also at E4, a handout detailing the benefits of increased dietary fiber intake, general dietary tips, and examples of high-fiber foods.

## Results

Recruitment began on February 12, 2025, and ended on September 1, 2025. We anticipate the intervention period will conclude in December 2025 and the observation period will conclude in March 2026.

As of September 22, 2025, 4947 patients have been screened for eligibility and 81 participants have been recruited to the study. A total of 72 participants have been officially enrolled and randomized. Progress through the phases of this planned randomized trial (enrollment, intervention allocation, follow-up, and data analysis) will be visually represented using the CONSORT (Consolidated Standards of Reporting Trials) flow diagram (see Figure 6).

**Figure 6. F6:**
[figure not shown]
CONSORT flow diagram depicting enrollment, allocation, follow-up, and analysis phases as of September 22, 2025.

## Discussion

This study proposes an mHealth intervention aiming to assist T2D patients in increasing their dietary fiber intake and possibly improving their glycemic control. In the management of diabetes, achieving glycemic control is critical for the prevention of complications, with a treatment goal of maintaining HbA_1c_ levels below 7% [15]. Despite advances in pharmacotherapy aimed at improving glycemic control, the increasing aging population with diabetes has raised concerns regarding the potential adverse effects and risks of polypharmacy associated with prolonged medication use [54]. The Diabetes Treatment Guide also specifies the need to continue lifestyle self-management such as diet and exercise regimens even when drug therapy is initiated [15]. This intervention could potentially enhance nutritional awareness and promote healthy eating habits among T2D patients.

The AI-assisted dietary fiber intervention was developed using a user-centered design approach, informed by recent formative research conducted before this study [35]. The formative research highlighted the usefulness of TPB in predicting intention to increase dietary fiber intake among individuals with T2D, with PBC and attitude emerging as significant predictors of this intention. These insights guided the design and refinement of the FiberMore intervention to better align with the needs and motivations of the target population. Previous meta-analyses have also demonstrated the capacity of the TPB to predict dietary behaviors [55,56]. We anticipate that the FiberMore intervention will increase PBC and attitude of patients toward fiber intake, which in turn will increase their intention and subsequently lead to increased fiber consumption.

The FiberMore intervention incorporates a personalized goal-setting approach, in which the user’s fiber goal increases gradually based on the number of days in the current week that the goal is successfully achieved. This approach is modeled after the success demonstrated in a previous study that used this goal-setting strategy, where incremental increases in step count goals were achieved and accompanied by corresponding growth in actual step count throughout the intervention period [20]. Additionally, during the first week of the intervention, intervention group participants will be given an initial fiber goal based on the 10th highest daily fiber intake achieved during the run-in period, to ensure that the initial fiber goal is achievable. As repeated failure to meet a goal can result in diminished confidence over goal achievement [57], the intervention begins with an easily attainable goal to foster a sense of success and strengthen participants’ perceived control over goal attainment. The goal-setting algorithm will then recommend gradual goal increments once participants successfully meet their fiber goals for at least 5 days in a week.

FiberMore allows users to add on additional information on the meal photos, such as the portion size of the food and details not visible in meal photos to enhance the accuracy of the nutrient estimation. Given that forgetting to photograph meals is a commonly reported issue in digital food logging using photography [58], the “chat a meal” feature provides an alternative way for participants to log their meals, thus reducing chances of missing meal records.

FiberMore is designed with patient safety in mind by minimizing gastrointestinal effects that may arise with increased dietary fiber intake. The intervention motivates study participants to increase their fiber in a gradual manner, rather than requiring a large amount of fiber intake all at once. This gradual approach allows the digestive system to adapt slowly to the increased fiber, thereby reducing the likelihood of gastrointestinal discomfort while allowing time to adjust to new eating habits. We have used prompt engineering to ensure that the maximum goal increase from the previous week’s goal is 2 g and cap the maximum fiber goal that can be set to 30 g per day.

One of the key features of this study is the use of salt reduction educational intervention as a “sham intervention” for the control group. Salt reduction education is a widely accepted strategy in the management of T2D [41]. It is anticipated that participation in a study will introduce biases that influence participant behavior, a phenomenon known as the “Hawthorne effect.” Intervention participants may be more conscious of their behavior if they believe that they are receiving a more beneficial intervention, while control participants may be less likely to comply with the trial protocol if they believe that they are not receiving active treatment [59]. Through the implementation of a sham intervention, the Hawthorne effect of receiving an intervention can be controlled [42]. We do not anticipate that the salt reduction educational intervention will have a significant impact on fiber consumption, as the educational content specifically focused on reducing sodium intake through cooking methods and seasoning practices, without targeting food choices related to dietary fiber.

To maintain blinding, participants will be informed that the study aims to assess the usefulness of a smartphone app in improving the eating habits of patients with type 2 diabetes. They will not be told that the intervention specifically targets increasing dietary fiber intake. Additionally, participants will remain unaware that they are randomly assigned to one of two groups. This approach helps mitigate social desirability bias, allowing for a more objective assessment of the intervention’s effects and enhancing the overall validity of the study’s findings.

Another key aspect of our approach is focusing exclusively on patients who are already motivated to change their behavior in dietary fiber intake. We achieve this by filtering participants based on their stage of change in TTM, targeting those in the contemplation, preparation, and action stages, which has shown to be effective [20,60]. Individuals who are already motivated to change need guidance and support to enhance their intentions and to translate their intentions into action, and they are more likely to engage with self-management tools [61]. In contrast, individuals with low motivation would require a fundamentally different intervention focused on enhancing motivation. Our strategy is supported by a study that reported 93.7% of T2D patients in Japan fall within these stages of dietary behavior change [62], suggesting that our intervention approach applies to a very large group of potential participants.

The study will maintain usual care practices for both the intervention and control groups. There will be no restrictions on medication adjustments or concurrent treatments during the study period. The intervention is aimed exclusively at improving dietary fiber intake, complementing the dietary counseling that T2D patients typically receive as a standard care practice in Japan.

This study is a multicenter randomized controlled trial, which enhances the generalizability of the findings to individuals with T2D across Japan. The elements of the intervention, such as the use of an AI-enabled chatbot to carry out personalized goal setting, barrier-solution planning, and meal logging are not unique to the Japanese context and can be adapted to other settings.

This study has several limitations. First, the findings may be specific to the studied population and may not fully generalize to other populations. Since the participants are likely to be older individuals of Japanese ethnicity, differences in lifestyles and the pathophysiology of T2D between Japanese and other populations may limit broader applicability. The cultural and dietary context of Japan may limit generalizability of the specific dietary patterns observed outside Japan. Additionally, the study is restricted to participants who can use smartphones; therefore, individuals with lower technological proficiency may be underrepresented. Individuals from lower socioeconomic backgrounds may have limited access to smartphones or may rely on older devices with limited functionality, which may result in selection bias that underrepresents these individuals.

AI performance in meal assessment can be significantly influenced by image quality, lighting conditions, and the angle at which the photo is taken [37]. Since participants use their own smartphones to capture meal images, variability in phone models and camera quality may introduce inconsistencies in photo quality. However, this approach closely mimics real-world conditions, making the findings more applicable to practical settings. To mitigate this variability, the study team provides detailed guidance and education to participants on how to take clear and well-angled photos to optimize AI performance.

Blinding of researchers is not considered in this study. Due to the complex nature of a dietary behavior change intervention that necessitates interactions between the researcher and participants, implementing researcher blinding is not feasible in this study, which may impose some degree of bias in the intervention delivery. The intervention content feedback and questionnaire reminders are delivered primarily by the app through prespecified algorithms and automated messages, thus minimizing researcher involvement in the intervention delivery. Furthermore, separate teams handle participant support and data management, and the statistician will remain blinded throughout the study.

The 24-week study involves multiple study events and intervention procedures, which may increase the risk of participant fatigue and dropout. We mitigate this by providing thorough explanation during study enrollment, along with a take-home manual containing detailed instructions on study procedures. To support adherence, we use SMS reminders and the LINE messaging app to notify participants of their hospital visits and intervention schedules. In addition, we align all study visits with routine hospital appointments, except for the single visit at official enrollment, thereby minimizing participant burden.

In this study, we will recruit T2D patients with an HbA_1c_ of at least 7.5%, thereby limiting the generalizability of the study findings to the broader T2D population. Nevertheless, as the treatment target for HbA1c is generally <7% according to the JDS guideline, this cut-off allows us to target patients who are most likely to benefit from additional dietary support. We also exclude patients with chronic kidney disease stage 4 and above to minimize the risk of potential hyperkalemia associated with fiber-rich foods, which may exclude a substantial portion of T2D patients.

Manual daily monitoring of the chatbot responses will be performed by the study team as a quality assurance measure, and to comply with ethics committee requirements. We acknowledge that this process may not be scalable in future larger-scale implementations. To address this limitation, future iterations of the system will explore the integration of automated monitoring features to reduce the burden on human resources.

The AI-based meal image analysis used to estimate dietary fiber and energy intake is not a validated gold-standard method, such as weighed food records, which may introduce bias in the dietary estimates. Nevertheless, our estimation approach is grounded in previous validation work comparing the AI model’s outputs to dietitian assessments, which demonstrated acceptable accuracy for fiber and energy estimation [39]. Furthermore, the same assessment method is applied uniformly to both the intervention and control group, so that any potential measurement error introduced by the AI model is unlikely to cause a bias to between-group comparisons.

We acknowledge that AI may misclassify food items and also portion sizes, which may introduce bias in the dietary estimates. These image recognition models are typically trained on datasets featuring popular or standardized foods, which may limit their ability to accurately classify ingredients in less common meals, such as regional specialties, traditional home-cooked dishes, or foods from rural areas. Nevertheless, the AI model used in this study has been fine-tuned using a dataset of real-world meal photos, resulting in improved accuracy in estimating dietary fiber content. Our fine-tuned AI model demonstrates better accuracy in estimating fiber and energy content from meal photos than dietitians, whose estimation capabilities are widely regarded as an acceptable standard for validating dietary intake [55]. Since our AI model exceeds expert-level accuracy in estimating dietary fiber and energy content from meal images, we believe that the model is sufficiently reliable for the purposes of this intervention.

This pilot RCT will provide important evidence on the efficacy, feasibility, and safety of an AI-based mHealth intervention in improving dietary fiber intake and glycemic control among free-living T2D patients. This pilot study offers valuable insights and evidence on the development of AI as a promising method for accurate, low-burden dietary assessment [37], including how participants engage with AI-based meal logging and respond to AI-driven diet intervention. Additionally, this study has the potential to generate a large volume of meal photos taken in real-world conditions, which can be leveraged for further fine-tuning and improving the AI model’s accuracy and performance in analyzing user-generated meal images.
